### **6.3 Study procedures**

#### **DATA COLLECTION**

##### **Medical records**

After patients have been included in the study, retrospective data from the patient's Electronic Medical Record (EMR) will be recorded: age, blood pressure (SBP / DBP) of the previous two consultations, prescribed medication, and if present, data concerning additional risk factors for CVD (number of minutes of exercise per week, diet, salt intake, smoking, alcohol consumption, height / weight, BMI, waist circumference, glucose and lipids (total cholesterol, HDL-cholesterol, TG, LDL), and co-morbid conditions in the patients history such as CVD (myocardial infarction, congestive heart failure, transient ischemic attack, stroke), kidney (renal failure, microalbuminuria), dementia, psyche (depression, schizophrenia), liver diseases.

##### *Pre and post-test*

Patients in the intervention group and the control group will participate in a series of pre- and a post-intervention measurements which will be conducted by a specially trained research nurse. Baseline measurements will take place as soon as possible (within two weeks) after inclusion and final measurements between four-to-six weeks after the patients' last educational session/ repeat prescription. All the measurements will be carried out in one of the four health care centers that participate in the study and, if possible, the health care center where the patient is registered. The measurement consists of: 1. A physical examination, 2. Identification of additional risk factors for CVD and 3. the administration of a questionnaire.

##### **Ad 1. Physical examination:**

Blood pressure: Systolic and diastolic blood pressure will be measured twice electronically, in patients who are seated with a 15 minute interval. The average of the two measurements will be recorded. (1)

Furthermore, weight, height and waist circumference will be measured (+ BMI calculated). The physical examination will be performed in a standardized way, in the health center where the patient is being treated. For these measurements, the protocol of the earlier SUNSET study will be used. (29)

##### **Ad 2. Additional risk factors for CVD**

Through a short questionnaire information will be collected about the current status of modifiable risk factors for CVD: number of minutes of exercise per week, diet, smoking, alcohol consumption. For this, questions from the SUNSET study will be used (29). Data on salt use are will be collected through a morning urine sample (lab-determination: Sodium and Creatinine).

##### **Ad 3. Interview**

The research nurse or interviewer will collect questionnaire data, immediately following the physical examination. The interview will take place in the participant's preferred language (English or Dutch). The interview includes questions about:

1. Adherence to treatment with regard to medication
2. Adherence regarding lifestyle advice.
3. Health: patients ideas about their own health.
4. Hypertension: ideas about hypertension and the causes, the way one deals with hypertension, motivation to do something about hypertension, confidence (self-efficacy) in managing ;hypertension.
4. Medication; ideas about medication in general, ideas about antihypertensive medications, experiences in taking antihypertensive medications, intentions (motivation) for following medication advice.
5. Lifestyle advice: ideas about lifestyle changes, acquired experience in dealing with lifestyle advice, intentions (motivation) on the compliance of lifestyle advice: This involves exercise per week, diet, salt intake, smoking and alcohol consumption.
6. Treatment: Satisfaction with treatment/care.

During the baseline assesment, the following demographics of the patient will be collected: age, gender, ethnicity (birth parents and grandparents; self-identification), education, occupation, income, marital status, duration of residence in the Netherlands, hypertension duration, health insurance. This part of the questionnaire will not be included in the post-test. During the post-test it will be assessed if stressful events have happened between account possible T0 and the final assessment. This information can be used in the final analysis of the data in order to assess potential confounders or effect modification (eg change in income, marital status).

Underneath we will provide more detailed information on the questionnaires that will be used in the interview. Where possible standardized validated questionnaires will be used:

1. To measure self-reported measure medication compliance, we will use the four-item scale Morisky. (30) To measure social support for adherence to treatment we will use the validated social support scale, from the MOS (Medical Outcome Survey) which had been used by Ogedebge (31) in a similar study.
2. To measure compliance with regard to lifestyle advice, we use a modified Morisky scale per lifestyle advice. (30)
- 3-5. To measure items that are mention in ad 3 to ad 5 above, we will use the High Blood Pressure Questionnaire (Utrecht University) that has been used in earlier Dutch research. (17,32) The High Blood Pressure questionnaire consists of components of validated international questionnaires: the Illness Perception Questionnaire (IPQ) which measures perceptions of disease, (33) the Beliefs about Medication Questionnaire, which measures perceptions on medication, (34,35 ) the Stages of Change Readiness and Treatment Eagerness Scale (SOCRATES) that measures behavioral intentions s, (36) a scale by Lorig measuring self-efficacy. (37) To the High Blood Pressure Questionnaire we will add a number of questions that are based on insights gained from our previous project Heebroedoe. (22-25) It is also possible that we choose a questionnaire which included similar elements and was previously used in the SUNSET study, conducted by the Department of Social Medicine of the AMC (29).
6. To measure satisfaction with care we consider using the Migrant QUOTE. (38) This is a validated questionnaire developed by NIVEL and the Department of Social Medicine of the AMC and which is adapted for use in migrants.

The selected questionnaires are, generally, not yet validated for the specific ethnic groups participating in this research. If we are still able find equivalent questionnaires that have been validated for non-Western populations, eg from the SUNSET study, we will prefer to select those questionnaires.

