#### **6.1.2. Secondary study parameters / endpoints (if applicable)**

Difference between baseline and 8 months past baseline regarding the following measures:

- Adherence to medication
- Adherence to lifestyle advice
- Mediating factors that may affect the way in which patients manage hypertension:
  - o beliefs about hypertension and medication / lifestyle changes
  - o motivation to use / medication to carry out lifestyle changes
  - o self-efficacy to use / medication to implement lifestyle changes
- Satisfaction with care
- Baseline demographics of potential confounders, such as age, gender, ethnicity, environment and other socio-economic circumstances are included in the study.

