### **8.3 Multivariate analysis**

Differences in the blood pressure values between treatment arms will be analyzed using a mixed model regression analysis that will take the dependence of the data and the intraclass correlation between centers into account. Corrections will also be performed for any differences in baseline characteristics of patients between the treatment arms.

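### Stressful events reported only at the post-test may be used as confounders or effect modifiers, which can bias the SBP effect if allocation changes the events or their reporting

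*Protocol*

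**What the plan says.** Section 6.3 (Ad 3. Interview) collects a demographic block at baseline that includes "education, occupation, income, marital status, duration of residence in the Netherlands, hypertension duration, health insurance". Of that block it says: "This part of the questionnaire will not be included in the post-test".

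The section then adds an item for the final visit only: "During the post-test it will be assessed if stressful events have happened between account possible T0 and the final assessment". The stated purpose is: "This information can be used in the final analysis of the data in order to assess potential confounders or effect modification". The examples in brackets are "eg change in income, marital status".

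The final visit comes after the whole intervention. Section 6.3 (Pre and post-test) sets "final measurements between four-to-six weeks after the patients' last educational session/ repeat prescription".

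Elsewhere the protocol links confounding to baseline data. Section 6.1.2 lists "Baseline demographics of potential confounders, such as age, gender, ethnicity, environment and other socio-economic circumstances are included in the study". Section 8.3, which describes the mixed model, says: "Corrections will also be performed for any differences in baseline characteristics of patients between the treatment arms".

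**The concern.** A confounder of a randomised comparison must precede the intervention. An event after T0 in a centre already allocated cannot have influenced the allocation. It can only be unrelated to it or be affected by it. If it is affected, adjusting for it removes part of the effect or brings in a bias through other causes of the event. Treating it as an effect modifier compares subsets of patients who are no longer comparable by randomisation.

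The more plausible route here is reporting. CAHE consists of three individual sessions that draw out patients' ideas and concerns and discuss the barriers they meet (section 5.1). That could change what a patient regards as stressful or chooses to mention. The blinding in section 6.2 covers the research nurse, the research assistant and data handling. It makes no claim about patients, who supply this variable. The questionnaire also follows directly on the physical examination, so the reports come after the outcome SBP has been taken. If patients learn their reading, which the protocol does not say, the outcome itself could colour the answers.

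At stake is the SBP estimate in any analysis that uses these reports, and with it the secondary comparisons, which section 8.2 says are analysed in the same way.

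**Working it through.** **The sections side by side**

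| Protocol section | Variable | Time of recording | Role |
|---|---|---|---|
| 6.1.2 | Age, gender, ethnicity, socio-economic circumstances | Baseline | Potential confounders |
| 6.3, Ad 3 | Stressful events since T0 | Post-test | May be used to assess confounding or effect modification |
| 8.2 | Ethnic group, gender | Baseline | Subgroups, with p value adjustment |
| 8.3 | Patient characteristics that differ between arms | Baseline | Correction in the mixed model |

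Only the 6.3 item is recorded after the intervention. Neither 8.2 nor 8.3 puts it in a model.

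**Size, as an illustration.** The protocol has no figure to reproduce. Its only relevant number is the target difference of 10 mmHg (section 4.4). Everything else below is assumed.

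Let d be the intervention-minus-control difference in the proportion reporting an event, and b the within-arm difference in SBP change (follow-up minus baseline) between reporters and non-reporters. With a negative effect meaning benefit:

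unadjusted effect = adjusted effect + d × b

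The size of the shift is therefore |d| × b:

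| Reporting difference (assumed) | b = 3 mmHg | b = 8 mmHg |
|---|---|---|
| 0 points | 0 | 0 |
| 10 points | 0.10 × 3 = 0.3 | 0.10 × 8 = 0.8 |
| 20 points | 0.20 × 3 = 0.6 | 0.20 × 8 = 1.6 |

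The range is 0 to 1.6 mmHg. Divided by 10 mmHg, that is 0 to 16% of the target difference. If reporters do worse and CAHE raises reporting, adjustment makes CAHE look better. If CAHE lowers reporting, adjustment makes it look worse.

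**Check by simulation.** One million simulated patients per setting, with an assumed direct effect of -10 mmHg, an event that adds 5 mmHg, and about 40% of controls reporting it. The last two columns add an unmeasured common cause of events and SBP (5 mmHg per SD).

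| Arm lowers event or report by | Unadjusted | Adjusted | Unadjusted, common cause | Adjusted, common cause |
|---|---|---|---|---|
| 0 points | -9.99 | -9.98 | -10.03 | -10.03 |
| 10 points | -10.50 | -10.01 | -10.50 | -9.68 |
| 20 points | -10.97 | -10.01 | -11.01 | -9.35 |

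Without a common cause the shifts are 0.01, 0.49 and 0.96 mmHg, matching d × b (0, 0.10 × 5 = 0.50, 0.20 × 5 = 1.00) up to simulation error. With a common cause they are 0.00, 0.82 and 1.66 mmHg, and the adjusted figure then equals neither the total effect nor the direct effect of -10. With no effect of arm on the event, the shift is nil in both settings.

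**The case against.** The strongest reply is that the protocol commits to nothing. The wording in 6.3 is permissive, and the planned estimates are an intention-to-treat difference in SBP change (8.2) and a mixed model with baseline corrections (8.3). A statistical analysis plan, if one exists, may label any use of these data as exploratory. This stands. It confines the risk to the optional use, and it means one cannot say from the protocol alone that the choice will be made after the results are known. It does not make the stated purpose right: calling post-allocation events potential confounders is an error in the protocol itself.

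Second, timing alone does not create bias, and hypertension education is unlikely to alter a patient's actual income or marital status, the only examples given. The interviewer is also meant to be blinded. This stands for true changes of that kind. It is weaker for perceived stress and for reporting, where the patient is the source.

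Third, with two centres per arm, outside events could differ between centres by chance, so recording them is sensible. That supports keeping the question and describing the answers. It does not support adjusting the main estimate, because the data cannot show that the reports are free of any effect of allocation.

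Two stronger readings are tempting:

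- A reader might infer that 6.3 contradicts 8.3. It does not. Section 8.3 plans a correction for baseline characteristics without expressly excluding further analyses.
- A reader might infer that changes in income or marital status cannot be known because the demographic block is not repeated. The patient can report such a change directly in answer to the stressful-events item, and a change since T0 could not be asked earlier.

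**Conclusion.** The concern holds in a limited form. Section 6.3 permits self-reported, post-allocation events to serve as confounders or effect modifiers. They cannot be confounders of the randomised comparison, and using them in either role can bias the SBP effect in either direction.

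The bias is conditional. It requires that CAHE changes the events or how they are perceived and reported, and also that reporters and non-reporters differ in SBP change. If either condition fails, the shift is zero.

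Under the assumed inputs the shift runs from 0 to about 1.6 mmHg (about 1.7 mmHg in the least favourable simulated setting). None of those inputs comes from the protocol, so the range is an illustration and not an estimate for this trial.

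The analyses as described in 8.2 and 8.3 are not affected. The point is modest, and worth correcting because the correction is so cheap.

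**What to change.** In section 6.3 (Ad 3. Interview), replace the stated use with wording to this effect:

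- Stressful events reported at the post-test are summarised descriptively by arm. At most they enter an analysis labelled exploratory, which does not replace the primary estimate.
- Covariates and effect modifiers for the SBP and secondary comparisons are limited to variables recorded at or before T0, in line with sections 6.1.2 and 8.3. Income and marital status at baseline remain available.

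The cost is a sentence or two of protocol text, with no change to data collection. The downside is that the events can no longer be used to adjust the main estimate, even if they turn out to differ between centres by chance. The descriptive summary would still show such a difference.

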#### *T1-T2-T3 measurement*

After the physical examination for the T0 assesment, three appointment will be made with patients in the intervention for the three CAHE sessions. A first after 2 weeks and on two subsequent times (intervals of 3 months).

After each session in patients in the intervention group blood pressure measurements performed by the treating POH (T1), (T2) (T3). In patients in the control group BP measurements will be conducted (after 3 ½ and 6 ½ months) by their treating POH in a standardized manner. On those occasions self-reported adherence to medication / lifestyle advice will also be measured with the Morisky scale and adapted Morisky scale, respectively. The treating POH will ask the patient to fill in this list in the waiting room

#### *Medication Use*

Besides self-reported medication adherence, medication adherence will also be evaluated using pharmacy data. Thereby the number of times in which a prescribed recipe for anti-hypertensives is picked up in time will be used as a measure. Thi9s indicates 'refill adherence ". Refill adherence is defined as the number of days for which antihypertensives are supplied divided by the total number of days after which the patient collects his/her repeat prescription). (39) A patient is defined as dherent if t he repeat prescription is filled within 7 days of the designated date. This method is also used in other research. (40)

#### *Process Data*

For process data on participation in the study and possible reasons for discontinuation of treatment in both study arms, the EMR data will be used. About 6-10 participants in the intervention group will be asked to participate in an in-depth interview. During the interview information will be collected on issues that have been tackled during CAHE and any obstacles that arose in these sessions.

About 6-10 participants from the control group will also be asked to participate in an in-depth interview to explore that experiences of barriers and facilitators for adhering to medication and lifestyle advice.

#### *Costs*

The consultations in the context of the intervention do not differ from the normal care and can be reimbursed by the patients'health insurance. When patients are not insured, an alternative solution for reimbursement will be sought.

To explore the personnel costs the intervention entails an the POH and other practitioners will be asked to record the time they spent on measurements and patient education. Time spent by health care professionals in the intervention and control group will be compared. Through the qualitative interviews with patients we will seek to get an impression of the costs patients had in participating in the intervention: indirect costs of participation in measurement and intervention sessions such as travel expenses or costs associated with lifestyle changes.

### **6.4 Withdrawal of individual subjects**

Participants can, as soon as they want, at any time, for any reason, withdraw from the study. This will not have any consequences for to their normal medical treatment and care. The researcher may decide, if necessary after consultation with the attending physician, to end the study participation of a patients for pressing medical reasons.

## **7 SAFETY REPORTING**

### **7.1 Section 10 WMO event**

In accordance to section 10, subsection 1, of the WMO, the investigator will inform the subjects and the reviewing accredited METC if anything Occurs, on the basis of Which it appears that the disadvantages of participation May Be Significantly greater than was foreseen in the research proposal. The study will be suspended pending further Top review by the accredited METC, except insofar as suspension would jeopardize the subjects' health. The investigator will take care That All subjects are kept informed.

### **7.2 Adverse and serious adverse events**

Adverse events are defined as any undesirable experience occurring to a subject during a clinical trial, Considered Whether or not related to the investigational drug. All adverse events reported spontaneously by the subject or observed by the Investiga → tor or his staff will be recorded.

A serious adverse event is any untoward medical occurrence or effect That at any dose results in death;

- Is life threatening (at the time of the event);
- Requires hospitalization or prolongation or Replace existing inpatients' hospitalization;
- Results in persistent or significant disability or incapacity;
- Is a congenital anomaly or birth defect;
- Is a new event of the trial likely to affect the safety of the subjects, zoals an unexpected outcome of an adverse reaction, lack of efficacy of an IMP used for the treatment of a life threatening disease, major safety finding from a newly completed animal study, etc.

All SAEs will be reported to the accredited METC That approved the protocol, According to the requirements of That METC.

### **7.3 Follow-up of adverse events**

All adverse events will be followed until they have abated, or until a stable situation has Reached leg. Depending on the event, follow up May require additional tests or medical procedures As indicated, and / or referral to the general physician or a medical specialist.

## **8 STATISTICAL ANALYSIS**

8.1 Descriptive statistics 8.2 Univariate analysis Multivariate analysis 8.3 8.4 Interim analysis (if applicable)

### **8.1 Descriptive statistics**

Quantitative data: Primary outcome measure: The main purpose of this study is to measure the effect of the intervention on systolic blood pressure in mmHg (difference between systolic blood pressure (SBP) measured at baseline and after 8 months)

Qualitative data: For a better understanding of the effects of the intervention a process evaluation was carried out, on the basis of the aforementioned qualitative data. This data will be transcribed in whole or in part. The analysis will be carried out using the computer analysis program MAXQDA, based on predefined questions and codes (framework analysis): topics that are addressed in intervention sessions; barriers that arise in these sessions; factors impeding or promoting adherence to medication and lifestyle advice; explanatory model of hypertension. Data on the number and reasons for refusals to participate in CAHE sessions or to terminate these sessions will be analyzed for frequency and content.

### **8.2 Univariate analysis**

Analysis of the primary outcome data: the systolic blood pressure measured at baseline minus the systolic blood pressure measured at 8 months past baseline.

All data entries will be controlled at random to avoid potentially incorrect codings. Univariate analyses will be conducted on the corrected database to compare variable distributions and identify positive or negative outliers. The analysis of the primary outcome measures will be carried out according to the 'intention to treat' principle. The primary outcome measure is calculated for each patient. Then the average within-group difference will be calculated for patients in the intervention group and the control group. Subsequently, the between-group difference between the calculated within-group differences will be calculated with a corresponding confidence interval. A decrease in systolic blood pressure by 10 mmHg (standard deviation = 15) in the intervention group as compared to the control group, with a confidence level of 5% probability of a Type 1 error, is considered to be clinically relevant. The analysis will use univariate and adjusted multilevel analysis.

The secondary data are analyzed in the same way.

If possible, separate subgroup analyses will be carried out by ethnic group and gender. For all analyses, a p value of 0.05 is used as the critical value. In subgroup analyses will be an adjustment to the p value for the number of analyses performed.

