### **4.4 Sample size calculation**

Four health care centers will be needed for the study and cluster-randomization. We assume a low between-cluster variance because of the homogeneity of demographic characteristics of the patient populations and treatment approaches of the participating health care centers. Based on the inclusion criteria and the fact that patients are treated according to the same clinical guideline (NHG), we assume little variation between the average blood pressures of hypertensive patients with an inadequately controlled BP. Because the intra-cluster correlation coefficient (ICC) is a ratio of the low between-cluster variation and within-cluster variation, we assume an ICC of  $< 3\%$ . The primary outcome measure will be a decrease in SBP at 8 months. A decrease of 10 mmHg (standard deviation = 15) in the intervention group compared to the control group will be considered as clinically relevant. To demonstrate this difference statistically with a reliability of the 5% chance of Type 1 error and a power of 80%, an average cluster size of 30 patients per cluster (health care centre) is needed. We strive to recruit a total 120 patients: 60 patients per treatment arm. Assuming an average dropout rate of 50%, 240 participants will have to be recruited.

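### Baseline systolic pressure is not a fixed covariate in the primary analysis: the protocol gives a raw change contrast and an unspecified adjusted model, and names neither as primary

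*Protocol*

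**What the plan says.** Section 8.2 takes as primary outcome "the systolic blood pressure measured at baseline minus the systolic blood pressure measured at 8 months past baseline". It averages this change within each arm, after which "the between-group difference between the calculated within-group differences will be calculated with a corresponding confidence interval". The same section adds: "The analysis will use univariate and adjusted multilevel analysis". It names no covariates and does not say whether the unadjusted or the adjusted result answers the primary objective.

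Section 8.3 describes the model: "Differences in the blood pressure values between treatment arms will be analyzed using a mixed model regression analysis", allowing for the correlation within centres. Its covariate rule is "Corrections will also be performed for any differences in baseline characteristics of patients between the treatment arms". Baseline SBP is not mentioned by name.

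Section 6.2 (Blinding) and section 6.3 (Pre and post-test, Physical examination) provide for SBP to be measured at T0 and at the final visit, in all participating centres, by a research nurse blinded to allocation.

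**The concern.** T0 SBP is likely to be among the strongest available predictors of 8-month SBP, and it is collected from everyone under blinded conditions. The written plan either subtracts it, which gives it a coefficient of exactly one, or lets it into a model only if the arms are seen to differ. Subtraction is less precise than regression adjustment whenever r is below 1. It also over-corrects: an arm that happens to start higher tends to show a larger fall with no treatment effect. With two centres per arm, a chance gap of a few mmHg at baseline is quite possible.

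Because neither analysis is named as primary, the choice between two estimates that can differ by a millimetre or two is open until the data are seen. A covariate list can wait for a statistical analysis plan. The point here is that the protocol itself states an estimator and an imbalance-driven rule, and both are weaker than the obvious alternative.

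**Working it through.** **Inputs.** From section 4.4: "A decrease of 10 mmHg (standard deviation = 15) in the intervention group compared to the control group will be considered as clinically relevant". The same section sets alpha at 5%, power at 80%, 30 evaluable patients in each centre (60 per arm) and an ICC below 3%. A two-sided test is assumed. The correlation r is not given and is taken as 0.3 to 0.8. The protocol does not say whether SD 15 refers to change or to a single reading.

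**The plan's own figure.** Two means, difference 10, SD 15, alpha 5%, power 80%: 35.3 per arm before clustering. The design effect is 1 + 29 x ICC. At ICC 0.024, 35.3 x 1.696 = 59.9, so 60 per arm is reproduced within the stated range. At the 3% ceiling, 35.3 x 1.87 = 66.0 per arm, and 60 give 76.1% nominal power.

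**Precision.** With equal variance s² at both visits, the change score has variance 2s²(1-r). Adjusted for baseline, the variance is s²(1-r²). The ratio is (1-r²)/(2(1-r)) = (1+r)/2.

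**Shift from a chance baseline gap.** For a gap D between arms, the unadjusted change contrast moves by (1-r)D. The standard error of D with baseline SD 15 is 15 x sqrt(2 x DEFF/60), where DEFF is the design effect: 2.7 mmHg at ICC 0 and 3.7 mmHg at ICC 3%.

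| r | variance ratio | n per arm, ICC 3% | nominal power with 60 per arm, ICC 3% | shift for one-SE gap, ICC 0 to 3% (mmHg) |
|---|---|---|---|---|
| change score | 1 | 66 | 76.1% | see below |
| 0.3 | 0.65 | 43 | 91.2% | 1.9 to 2.6 |
| 0.5 | 0.75 | 50 | 86.9% | 1.4 to 1.9 |
| 0.7 | 0.85 | 57 | 82.5% | 0.8 to 1.1 |
| 0.8 | 0.90 | 60 | 80.4% | 0.5 to 0.7 |

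Rows with an r value give sample size and power for the baseline-adjusted analysis. The last column is the shift in the unadjusted change contrast at that r, which adjustment removes.

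Sample size and power take 15 as the SD of change; the shift takes 15 as the SD of a single reading. Both hold together only at r=0.5. If 15 is instead the SD of a single reading, nominal power with 60 per arm at ICC 3% is 61.7%, 76.1% and 93.2% for the change score at r = 0.3, 0.5 and 0.7, against 79.9%, 86.9% and 96.2% with adjustment. All these powers use a normal approximation and ignore the small number of clusters.

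**Against an imbalance-triggered rule.** 10,000 trials were simulated with four centres of 30, r=0.5, ICC 3% and SD of change 15, the same r holding between and within centres. The trigger was a patient-level baseline test at p<0.05. This trigger is an assumption, since section 8.3 sets no threshold.

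- SD of the effect estimate: 3.74 (change score), 3.45 (adjust only if p<0.05), 3.25 (always adjust).
- Gain of always adjusting over the triggered rule: 1 - 3.25²/3.45² = 1 - 10.56/11.90 = 11% of variance.
- Mean error when the intervention arm starts 3 to 7 mmHg higher, in the direction of a larger apparent fall in that arm: 2.3, 1.5 and about 0 mmHg.
- Averaged over all simulated trials, the change score shows no bias (mean error 0.04 mmHg).

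**The case against.** A reader might infer that the primary analysis is biased by regression to the mean because patients are selected for raised pressure. The documents do not support that. Regression common to both arms cancels in the between-arm contrast. The (1-r)D shift needs only r below 1, not selection, and it averages to zero over randomisation. Section 9.2 also selects patients from medical records before T0, so some of the regression may be over by the time T0 is measured.

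A reader might also infer that the raw change score is the sole primary analysis, or that SBP is expressly adjusted for only if it differs. Section 8.2 also announces an adjusted multilevel analysis, and section 8.3 speaks of baseline characteristics without naming SBP. If SBP counts as one, section 8.3 may correct the very imbalance described, and its wording covers any difference, with no significance threshold. The full shift then belongs only to the unadjusted contrast. Nor do 8.2 and 8.3 contradict each other outright: a mixed model on pressure values can estimate a difference in change.

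The size is uncertain too. The correlation is assumed, 3% is the ICC ceiling, and at r=0.8 the variance saving is only 10%.

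All of this stands, and it limits the claim. It leaves two facts in place: no primary analysis is named, and adjustment for T0 SBP is either data-dependent or absent, depending on how section 8.3 is read. Always including T0 SBP is the better rule on either reading.

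**Conclusion.** The point holds as one of precision and prespecification. Always adjusting for T0 SBP lowers the variance to 0.65 to 0.90 of that of the change score for an assumed r of 0.3 to 0.8, assuming equal variances at both visits. Compared with a p<0.05 trigger, which the protocol does not state, the gain is about 11% at r=0.5. It also removes a conditional shift in the unadjusted contrast of about 1.4 to 1.9 mmHg for a one-standard-error gap at r=0.5, or 0.5 to 0.7 mmHg at r=0.8, against a 10 mmHg target (baseline SD 15, ICC 0 to 3%). This is not bias over randomisation, although only one allocation of four centres will be realised.

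It would be wrong to read the power gains as a rescue of the design. Four clusters remain the dominant limit: with a t reference on 2 degrees of freedom, change-score power at 60 per arm is only about 33% (ICC 3%) to 43% (ICC 1%).

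**What to change.** Name one primary analysis in sections 8.2 and 8.3: a mixed model of 8-month SBP on arm and T0 SBP, with a random centre effect. Using change as the outcome with the same covariates gives the same arm effect, apart from the sign convention, so the wording of the objective can stay.

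- Include T0 SBP whatever imbalance is observed, and drop the imbalance-triggered rule for it.
- Use the research nurse's T0 reading as the covariate, not values from the medical record.
- Keep the unadjusted difference in mean change as a sensitivity analysis, labelled as such.
- State whether the SD of 15 in section 4.4 refers to change or to a single reading.

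The cost is wording only, because T0 SBP is already scheduled for every participant. The change does not address the small number of clusters, which needs separate treatment.
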